#### Trial timescales

At the current rate of patients presenting to the centers, relatively broad inclusion criteria, and experience from previous trials of this nature, this study is expected to be completed within approximately twelve months (Fig. 2, Additional file 1. SPIRIT Checklist for Trials).

**Fig. 2 Fig2:**
[figure not shown]
Standard Protocol Items: Recommendations for Interventional Trials (SPIRIT) flow sheet schedule of enrolment, interventions and assessments. VAS visual analogue scale, AVVQ Aberdeen Varicose Vein Questionnaire, VCSS Venous Clinical Severity Score

#### Baseline

Each center will have two permanent medical staff to gather information and conduct follow-ups, an investigator to collect information, and a checker to evaluate the quality of questionnaires and patient cooperation. All investigators will be trained before the official follow-up. At baseline, primary demographic data will be collected for each patient. Patients’ contact details will also be collected to enable the scheduling of follow-up appointments. Patients will be asked to record pain scores with VAS, fill out a quality of life questionnaire (AVVQ), and assess their clinical scores (CEAP and VCSS). They will also be asked to attend a follow-up in 1 week and at 3 months.

#### Follow-up

Patients will be followed up in the outpatient clinic at 1 week and 3 months. At the 1 week follow-up, patients will be asked to record pain scores with VAS, fill out a quality of life questionnaire (AVVQ), and will have their clinical scores assessed (VCSS). They will also be asked how soon they could return to regular work, postoperative complications, and compliance with the intervention. A venous Duplex scan will be held to determine the occlusion of the target vein. Follow-up at 3 months after thermal ablation will be the same as at 1 week follow-up.

#### Sample size and study duration

According to the literature [29–31] and clinical experts’ recommendations, the target vein occlusion rate in the control group (group B) was set to 98%, and a non-inferiority threshold δ of − 6% was taken [17]. With a power of 90% and 2.5% (unilateral) significance equivalence, a minimum of 230 patients (115 per group) will need to be recruited. However, considering a potential drop-out rate of 20%, combined with the low probability of adverse events in this trial, the total sample size was expanded to 360 patients. With 3 months follow-up, the study will run for 12 months.

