**Methods:**

A prospective, multicenter, non-inferiority randomized controlled trial is designed to evaluate the non-inferiority of target vein occlusion rate at 3 months. Three hundred and sixty patients will be randomly assigned in a 1:1 ratio to one of the following treatments: (A) 3 M™ Coban™ elastic bandage for 48 h or (B) 3 M™ Coban™ elastic bandage for the first 24 h and then a class II compression full-length stocking (23–32 mm Hg) for 1 week. The two groups will be compared on several variables, including target vein occlusion rate at 3 months (primary outcome indicator), pain, quality of life, clinical severity of varicose veins, postoperative complications, time to return to regular work, and compliance.

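### The 230 patients said to give 90% power at one-sided 2.5% give about 73% with a test that holds that level; the step to 360 is not derived, and 360 less the planned 20% loss gives 84% to 86% depending on the method

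*Protocol article*

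**What the plan says.** All the sizing figures are in the protocol article, section Sample size and study duration:

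- Control rate: "the target vein occlusion rate in the control group (group B) was set to 98" per cent. No expected rate is given for group A.
- Margin: "a non-inferiority threshold δ of − 6% was taken".
- Error rates: "With a power of 90% and 2.5% (unilateral) significance equivalence".
- Result: "a minimum of 230 patients (115 per group) will need to be recruited".
- Enlargement: "considering a potential drop-out rate of 20" per cent, together with an expectation that adverse events will be rare, "the total sample size was expanded to 360 patients".

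Allocation is 1:1 (abstract, Methods), so 360 means 180 per arm. The Statistical analysis section requires non-inferiority in both the intention-to-treat and the per-protocol set. It gives chi-square or Fisher's exact test for categorical data in general and no specific method for the non-inferiority comparison.

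**The concern.** The section promises two properties together at 115 per group: 90% power and a one-sided error of 2.5%. At a 98% success rate only about two failures are expected in each arm, and the usual normal approximation for a difference in proportions is poor there. If it fails, the promised power is reached only by a test that exceeds its level, or the level is kept only at lower power.

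The target of 360 is offered without a power of its own. Its two stated reasons are a drop-out allowance that yields a different number and a remark on adverse events that does not enter the calculation for occlusion. A reader therefore cannot tell what power the trial has at its actual size, or after the loss it plans for. This matters most for the per-protocol set, which must also succeed and which excludes patients who drop out or deviate.

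**Working it through.** **Inputs** (Sample size and study duration): control rate 0.98, margin 0.06, one-sided α = 0.025, power 0.90, drop-out 20%. The group A rate is assumed to be 0.98, since equal rates reproduce the stated figure.

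**1. The plan's own figure.** Unpooled Wald formula:

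n per arm = (1.960 + 1.2816)² × 2 × 0.98 × 0.02 / 0.06² = 10.507 × 0.0392 / 0.0036 = 114.4, rounded up to 115, or 230 in total.

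The figure reproduces exactly. Approximate power by the same formula at 115 is 90.1%.

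**2. Is the approximation sound here?** Expected failures per arm are 115 × 0.02 = 2.3. Power at 98% v 98% and error at 92% v 98% were therefore computed by summing exact binomial probabilities over all possible results. The maximum error is taken over control rates from 90% to 100%.

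| Rule, 115 per arm | Power | Error at 92% v 98% | Maximum error |
|---|---|---|---|
| Wald | 89.1% | 4.7% | 8.1% |
| Wald, continuity-corrected | 80.6% | 2.2% | 3.4% |
| Agresti-Caffo | 83.3% | 3.0% | 3.6% |
| Farrington-Manning | 73.2% | 1.9% | 2.5% |
| Newcombe | 73.5% | 2.2% | 2.5% |

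An exact unconditional test on the score statistic also has 73.2% power. No rule examined gives both 90% power and 2.5% error at this size. With the score test, the chance of missing true non-inferiority is 100 − 73.2 = 26.8%, against the 10% stated.

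**3. From 230 to 360.** 230 / (1 − 0.20) = 287.5, so 288. A total of 360 exceeds this by 72. Read as a pure loss allowance, it would correspond to 1 − 230/360 = 36.1%.

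**4. Power at the actual target.** 360 × 0.80 = 288, or 144 per arm; 360 × 0.90 = 324, or 162 per arm.

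| Evaluable per arm | Farrington-Manning | Newcombe |
|---|---|---|
| 144 (20% loss) | 84.0% | 86.1% |
| 162 (10% loss) | just under 90% | just under 90% |
| 180 (no loss) | 92.4% | 92.4% |

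The exact unconditional test has 82.8% at 144 and 92.4% at 180. By the Wald formula the plan appears to have used, 144 per arm would show 95.3%, so that formula hides the shortfall.

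Exact power rises in a sawtooth. Farrington-Manning has 91.2% power at 170 per arm and 89.5% at 165, so about 170 evaluable per arm are needed for 90%. That is 340 of 360, a loss of 20/360 = 5.6%.

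**The case against.** The strongest reply is that nothing has been miscalculated. The 230 follows from the stated inputs by a standard formula. The non-inferiority method may be fixed in an analysis plan that is not shown, and with a Wald test exact power at 115 per arm is 89.1%, close to the claim. This stands in part: the 73% is conditional on using a test that holds its level. But the section states 2.5% alongside 90%, and the Wald rule misses the 2.5%. The criticism is of the approximation, not of the arithmetic.

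Three stronger readings are tempting, and the documents do not support them.

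- **That 360 is a wrong value of 230/0.8.** Because 288/0.8 = 360, a reader might infer that the 20% was applied twice. The article never presents 360 as 230/0.8. It gives a second reason, unquantified though it is, and the excess over 288 is on the safe side: after 20% loss, 288 remain against a stated minimum of 230. The supportable point is that the step is not derived.
- **That the sponsor might stop at 230.** The abstract and the sample-size section both set 360 as the target, and nothing provides for stopping short of it.
- **That the trial is badly underpowered as designed.** With all 360 evaluable, power is 92%. The shortfall appears as losses grow towards the planned 20%.

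**Conclusion.** The point holds in a limited form. The 230 is correctly computed from the Wald formula, but it does not deliver 90% power at a true one-sided 2.5%. Level-holding methods give about 73% there, and the Wald rule has a true error of about 4.7% at 92% v 98%. The target of 360 is conservative against the stated minimum but not derived. At the plan's own 20% loss it gives 84% (Farrington-Manning) or 86% (Newcombe), that is, 4 to 6 points below 90%. With 10% loss it is about 90%, and with none 92%.

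These figures assume a true rate of 98% in both arms (the group A rate is not stated), equal loss in the two arms, and each analysis set taken alone. Requiring success in both sets cannot raise power. The size of the shortfall depends on the method finally used. The design is close to adequate; it is the stated power that needs correcting.

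**What to change.** Keep 360 and change the text:

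1. State the assumed rate in group A, and no longer present 230 as the number that gives 90% power.
2. Name one level-keeping method, for example the Farrington-Manning score test with its interval, for both the sample size and the primary non-inferiority analysis. If the analysis plan already names such a method, use that one in the sample-size section.
3. Give the power for that one method. For Farrington-Manning with 98% in both arms: 360 randomised gives about 92% power with no loss, 90% with 10% loss and 84% with 20% loss (288 evaluable). The 86% belongs to Newcombe and should not be combined with the score result as a range for one method.
4. Drop the adverse-event reason for the enlargement, or explain what it contributes.

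The cost is wording only. The stated power becomes slightly less favourable, and no extra patients are needed.

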#### Recruitment

Recruitment will occur in outpatient clinics at each center; patients who meet the inclusion criteria will be made aware of this study and provided with the appropriate information. Patients expressing an interest in participation will be offered an appointment for a screening visit with a study investigator/ a doctor. After taking a detailed medical history and a detailed duplex ultrasound examination, if the potential participant meets the criteria and is willing to proceed to enrolment in the trial, they will sign informed consent forms. Here the potential participant will be fully briefed on the trial process, the treatments, risks, economic compensation, and follow-up.

#### Statistical analysis

Continuous data will be compared by the Student *t*-test or Mann–Whitney *U* test for parametric and non-parametric data, as appropriate. Categorical data will be compared by the chi-square test or Fisher’s exact test, as appropriate. Considering the participants might crossover or be lost to follow-up, we will test non-inferiority using two analysis sets. One is the intention-to-treat set, considering all patients as randomized regardless of whether they received the randomized treatment, the other is the per-protocol set. We propose declaring short-term compression therapy non-inferior to long-term compression therapy, only if shown to be non-inferior using both the “intention-to-treat” and “per-protocol” analysis sets. *P* < 0.05 will be considered statistically significant, and all data will be analyzed using SAS 9.2 software.

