### Objectives

The study’s primary objective is determining the target vein occlusion rate at 3 months, assessed with a Duplex ultrasound scan. Recanalization will be defined by a segment of the vein ≥ 5 cm. Secondary objectives are to compare the two treatment groups for pain scores at baseline, 1 week, and 3 months using a visual analog scale (VAS); quality of life scores at baseline, 1 week, and 3 months using the AVVQ (Aberdeen Varicose Vein Questionnaire); clinical change using the VCSS (Venous Clinical Severity Score) at baseline, 1 week, and 3 months; postoperative complications including edema, ecchymosis, paresthesia, skin burn/discoloration, phlebitis, hematoma, infection, deep vein thrombosis, and pulmonary embolism; time is taken to return to routine work; patient compliance with the intervention assessed with a questionnaire.

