#### Participants

This trial was conducted in patients with primary varicose great saphenous veins of lower extremities diagnosed in nine target hospitals from April 2023 to August 2023. All participants included in the trial signed an informed consent form.

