#### Randomize and blinding

Patients will be randomized (using a random number table generated by the Excel RANDOM function) to group A or B. A fixed data analyst will generate the table of random numbers via computer. The randomization scheme will be hidden from doctors and patients. Since the intervention in this trial could not blind the doctors and patients, only the data analyzers were blinded.

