#### Description of intervention

Before compression therapy, all patients will undergo a standard thermal ablation procedure (RFA, Medtronic Closure Fast or EVLA, Eufoton 1470 nm ring laser). Patients will be randomized to groups A or B. Patients randomized to group A will be asked to wear the 3 M™ Coban™ elastic bandage for 48 h after the surgery. Patients randomized to group B will be asked to wear the 3 M™ Coban™ elastic bandage for 24 h and then a class II compression full-length stockings (23–32 mmHg) day and night time for 1 week (Fig. 1). The surgeon will place the bandages on the patient's leg while still lying on the operating table after thermal ablation. By the way, implementing short-term or long-term compression therapy will not require alteration to usual care pathways (including the use of any medication) and these will continue for both trial arms.

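### Pain, quality of life and venous severity are measured at baseline, but the named tests take no baseline covariate, which gives up precision in three secondary outcomes

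*Protocol article*

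**What the plan says.** The Statistical analysis section of the protocol article sets one rule for all continuous outcomes: "Continuous data will be compared by the Student" t-test, or by the Mann–Whitney U test where a non-parametric method is needed. No covariate or regression model is named.

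The three scales have baseline values. The Baseline section has patients "record pain scores with VAS, fill out a quality of life questionnaire (AVVQ), and assess their clinical scores (CEAP and VCSS". The Follow-up section repeats VAS, AVVQ and VCSS at 1 week and again at 3 months. The Objectives section lists the same three times for each scale. For VCSS alone it uses the language of change: "clinical change using the VCSS (Venous Clinical Severity Score) at baseline, 1 week, and 3 months". Nowhere does the article say whether the tests are applied to follow-up scores or to changes from baseline.

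**The concern.** A two-sample test of a follow-up score leaves unused the part of the between-patient variation that the baseline score explains. The trial collects that score anyway, so the loss is avoidable.

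These outcomes matter to how the result will be read. The Background motivates the trial with studies in which stockings reduced first-week pain, and the Discussion looks to better quality of life with a simpler regimen. If the 48 h bandage carries a pain penalty, the precision of the VAS comparison decides how well the trial can show it or limit its size. An imprecise comparison that misses significance could be taken for evidence of no penalty.

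A chance difference between the arms at baseline would also pass in part into an unadjusted comparison of follow-up scores.

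**Working it through.** **The plan's own figure.** The sample size rests on the primary outcome: 98% occlusion in both arms (the article states it for group B; equality is assumed for group A), margin 6 points, one-sided 2.5%, power 90%. With unpooled variance,

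n per arm = (1.960 + 1.282)² × 2 × 0.98 × 0.02 / 0.06² = 114.4, rounded up to 115, or 230 in total.

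This reproduces the stated minimum. No continuous score enters it, so the point made here cannot alter it.

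**Inputs for the secondary scales.**
- 360 patients allocated 1:1 (Abstract), so 180 per arm.
- 20% drop-out (Sample size and study duration), so 180 × 0.80 = 144 per arm at follow-up.
- Two-sided 5% (the article gives P < 0.05; two-sided is assumed) and 80% power, chosen for illustration.
- Correlation r between baseline and follow-up: not in the documents, assumed from 0.1 to 0.7.
- A linear relation with a common slope and, for change scores, equal SDs at baseline and follow-up (assumed).

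**Formulas.** Relative to a t-test of follow-up scores, the variance of the treatment difference is 1 − r² for ANCOVA and 2(1 − r) for a t-test of change scores. ANCOVA relative to change is therefore (1 − r²) / [2(1 − r)] = (1 + r)/2. The equivalent sample-size ratio is 1/(1 − r²).

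Without adjustment, the detectable difference is (1.960 + 0.842) × √(2/144) = 0.330 SD. With ANCOVA it is 0.330 × √(1 − r²).

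| Assumed r | Variance cut by ANCOVA | Equivalent extra patients | Detectable difference (SD) | Power where unadjusted is 80% | ANCOVA variance ÷ change-score variance |
|---|---|---|---|---|---|
| 0.1 | 1% | 1% | 0.329 | 80.4% | 0.55 |
| 0.3 | 9% | 10% | 0.315 | 83.6% | 0.65 |
| 0.5 | 25% | 33% | 0.286 | 89.9% | 0.75 |
| 0.7 | 49% | 96% | 0.236 | 97.5% | 0.85 |

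ANCOVA is more efficient than either form of the t-test at every r in the table. The gain over follow-up scores grows with r, and the gain over change scores shrinks with r.

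**Chance imbalance.** With 180 per arm, the standard error of a baseline mean difference is √(2/180) = 0.105 SD, a 95% range of ±0.21 SD. An imbalance of 0.2 SD, near the edge of that range, would move an unadjusted follow-up difference by r × 0.2: 0.02, 0.06, 0.10 or 0.14 SD at r = 0.1, 0.3, 0.5 or 0.7. The unadjusted standard error already allows for this on average. It is the same loss seen within one realised trial, and should not be added to the variance loss in the table.

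**The case against.** The strongest reply is that nothing is invalid. Under randomization the t-test and the Mann–Whitney test keep their type I error and are unbiased on average, so adjustment is a matter of efficiency. That is right, and it sets the severity.

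The text also does not say that follow-up scores are what is tested. A t-test on change scores uses the baseline and is not excluded, least of all for VCSS. This stands, but it does not remove the point, because change scores are also less efficient than ANCOVA.

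The size of the gain is uncertain. Baseline VAS is pain before the procedure, while VAS at 1 week reflects recovery from it. The correlation could be low, and at r = 0.1 the gain is only 1%. The table compares ANCOVA with t-tests; no figure is offered against Mann–Whitney.

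One could also say that the choice of model belongs in a statistical analysis plan. Silence would be no fault, but the article does name a method for these outcomes, and that method has no place for a covariate.

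A reader might go further and infer that allocation was unstratified and that centre and device are wrongly left out. The article mentions patients "diagnosed in nine target hospitals from April 2023 to August 2023", two ablation techniques ("RFA, Medtronic Closure Fast or EVLA, Eufoton 1470 nm ring laser"), and allocation "using a random number table generated by the Excel RANDOM function". The last phrase gives the source of the random numbers and says nothing for or against blocks or strata. The article is a condensed account, and its publication section says that the full protocol is available on request. Nor would leaving these factors out be an error if allocation was in fact unstratified. The stronger reading is not supported.

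**Conclusion.** The point holds as a minor loss of efficiency in VAS, AVVQ and VCSS. Relative to a t-test of follow-up scores, baseline adjustment would reduce the variance by 1% to 49% for an assumed correlation of 0.1 to 0.7, with 25% at 0.5. Relative to a t-test of change scores, the reduction would be 45% to 15% over the same range. The true figure depends on a correlation that the documents do not give and that may differ between scales and visits.

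It would be wrong to infer bias, an inflated error rate or a threat to the trial's main conclusion. The primary outcome is binary, its non-inferiority test is untouched, and the sample size of 230 reproduces and stays as it is.

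**What to change.** In the Statistical analysis section, replace the t-test or Mann–Whitney rule for VAS, AVVQ and VCSS with one of the following:
- ANCOVA at 1 week and at 3 months, with arm and the baseline score of the same scale; or
- a mixed model for both visits, with arm, visit, arm-by-visit interaction and baseline score.

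Report adjusted mean differences at each visit with 95% confidence intervals. State whether allocation was stratified by centre or ablation device; if it was, include those factors in the model.

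The cost is a sentence or two in the plan and a few lines of code. No new data are needed, since all three baseline scores are already collected. The change should be recorded before the analysts are unblinded.

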**Discussion:**

Suppose the effect of the 3 M™ Coban™ elastic bandage for 48 h proves to be non-inferior to long-term compression therapy. In that case, this short-term treatment may contribute to a future update of clinical guidelines for compression therapy after thermal ablation of varicose veins, resulting in higher patient compliance and better postoperative quality of life.

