#### Secondary outcomes

The secondary outcomes include the following:PainPatients will be asked to record pain scores with VAS, and the scale ranges from 0 (no pain) to 10 (worst pain imaginable) [26].Quality of lifePatients will be asked to fill out the AVVQ to measure the health status of varicose vein patients based on symptoms and impact on daily activities. A total score ranging from 0 to 35, with 35 being the worst quality of life [27].Venous clinical severityPatients will be asked to fill out the VCSS to evaluate the severity of the hallmarks of venous disease. The questionnaire consisted of ten questions, each of which was answered by 0 (none), 1 (mild), 2 (moderate), and 3 (severe)—a total score ranging from 0 to 30, with 30 being the worst quality of venous disease [28].Postoperative complicationsPostoperative complications include postoperative edema, ecchymosis, sensory abnormalities, skin burns/discoloration, phlebitis, hematoma, infection, deep vein thrombosis, and pulmonary embolism.Time to return to regular workThe investigator will use a uniform question to ask the patient how long it takes to return to regular work, life, or both (days), and then record.ComplianceCompliance refers to the extent to which patients follow compression therapy as recommended by their clinicians. Investigators will ask patients whether they have completed compression treatment as recommended by their doctors in the past week or 3 months. The answer to this question involves 1 (none), 2 (occasionally), 3 (mostly), and 4 (entirely). Those who still need to fully follow the study protocol for compression treatment should continue to be asked about their actual compression treatment and recorded.

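### Compliance is an ordered four-level secondary outcome, but the analysis rule, read naturally, sends it to an unordered chi-square or Fisher test that does not ask which arm complied better

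*Protocol article*

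**What the plan says.** Under Secondary outcomes, the protocol article has investigators ask patients whether they completed compression as advised: "The answer to this question involves 1 (none), 2 (occasionally), 3 (mostly), and 4 (entirely". The codes 1 to 4 rise with compliance. Under Follow-up, the question is put at 1 week and again at 3 months.

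The Statistical analysis section gives two general routes. The first begins "Continuous data will be compared by the Student" and names the *t*-test or the Mann–Whitney *U* test. The second reads "Categorical data will be compared by the chi-square test or Fisher’s exact test, as appropriate". The threshold is P "< 0.05 will be considered statistically significant". No outcome is assigned to a route by name, and no test for ordered categories appears.

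The Discussion part of the abstract says what non-inferiority of the short regimen might lead to: "resulting in higher patient compliance and better postoperative quality of life".

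**The concern.** A single question with four answer categories is categorical data in ordinary usage, so the stated rule points to a 2 × 4 chi-square or Fisher test. With all four levels in use, the chi-square version has 3 degrees of freedom. Either test returns the same P-value if the four answers are relabelled in any order.

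The article's interest in compliance is directional: it hopes the shorter regimen is followed better. An unordered test does not address that. It spends degrees of freedom on patterns nobody is asking about. A small P-value could also come from an arm with more *none* and more *entirely* answers at once. What is at stake is the chance of detecting a real compliance gain, and how clearly a positive result can be read. The primary non-inferiority conclusion is not at stake.

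**Working it through.** **Plan's own figure.** Sample size and study duration states: "With a power of 90% and 2.5% (unilateral) significance equivalence, a minimum of 230 patients (115 per group) will need to be recruited". With 98% occlusion in both arms and a 6-point margin, n = (1.960 + 1.282)² × 2 × 0.98 × 0.02 / 0.06² = 10.51 × 0.0392 / 0.0036 = 114.4, so 115 per group. This reproduces, but it concerns the primary outcome. No power or effect is stated for compliance.

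**Inputs from the article.**
- Allocation: "randomly assigned in a 1:1 ratio to one of the following treatments".
- Size: a total of 360, reached by a dropout allowance of 20% (Sample size and study duration). Patients with data per arm: 360 × 0.80 / 2 = 144.
- Level: 5%. Two-sided is assumed, because the article does not state sidedness for secondary tests.

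**Inputs assumed.** The answer distribution in group B, and a uniform shift in group A. For each cut-point k, the odds of answering k or lower in group A equal those in group B divided by a common odds ratio (OR).

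**Step 1: one case by hand.** Take group B at 5/15/30/50% over levels 1 to 4 and OR 1.75.
- Cumulative odds in B: 0.0526, 0.25, 1.
- Divided by 1.75: 0.0301, 0.1429, 0.5714.
- Group A is therefore 2.9/9.6/23.9/63.6%.
- Pearson noncentrality = n Σ (pA − pB)² / (pA + pB) = 144 × (0.0055 + 0.0120 + 0.0070 + 0.0164), about 5.9. With 3 df this gives power of about 51%.

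**Step 2: simulation.** 10,000 to 20,000 trials per scenario, 144 per arm, Pearson chi-square against the tie-corrected Mann–Whitney test. The Monte Carlo standard error of each power is at most √(0.25/10,000) = 0.5 points.

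| Group B (%) | OR 1.5 | OR 1.75 | OR 2.0 |
|---|---|---|---|
| 5/15/30/50 | 28 vs 43 | 51 vs 68 | 70 vs 84 |
| 10/20/30/40 | 31 vs 46 | 55 vs 72 | 75 vs 88 |
| 2/8/20/70 | 21 vs 33 | 37 vs 54 | 53 vs 70 |
| 5/10/15/70 | 22 vs 34 | 37 vs 53 | 53 vs 71 |

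Each cell is power in per cent, chi-square vs Mann–Whitney. Allowing for simulation error, the loss is about 11 to 18 points. At OR 2.5 it is about 4 to 14 points over the same four distributions. With no difference between arms, both tests reject in about 4 to 5% of trials.

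**Step 3: sensitivity to the assumed distribution.** A more top-heavy group B (2/5/13/80%) loses 9.5 points at OR 1.5, 18 at OR 2.0 and still 18 at OR 2.5. An even one (25% at each level) loses 15.5, 12 and 3 points at the same odds ratios.

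**Step 4: general check.** For a shift fully captured by a 1-df ordered test, the same noncentrality on 3 df lowers power from 70% to 53%, from 80% to 64.5% and from 90% to 78%. These are losses of 17, 15.5 and 12 points.

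**Step 5: shifts that are not uniform.**
- Movement only from *mostly* to *entirely* (5/15/30/50 to 5/15/15/65, 144 per arm): chi-square 77%, Mann–Whitney 51%.
- Movement to both extremes (5/15/40/40 to 12/8/25/55, 180 per arm): chi-square 97%, Mann–Whitney 47%.

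**The case against.** - **The rule is generic.** The article never says that compliance goes to chi-square or Fisher. The item is coded 1 to 4, and Mann–Whitney is named in the same section. This stands in part: the routing is an inference. It remains the natural one, because Mann–Whitney is offered only for continuous data.
- **Matching each outcome to a test can be left to an analysis plan that is not shown.** That is fair as to missing detail. The point here is that the rule the article does state fits this outcome badly. If a fuller plan already assigns an ordered test, the point falls away.
- **The power loss is assumed.** This stands. A reader might infer that the plan as written costs 12 to 18 points of power. The article supports no such fixed figure, since it gives neither a compliance distribution nor an effect. If the gain is large, little is lost: with 90% vs 70% answering *entirely*, a simulation at 144 per arm gave 97% for chi-square and 99% for Mann–Whitney. If the shift is not uniform, the unordered test can win.
- **Fisher's exact test was not simulated.** This stands. At 2% *none* the expected count is about 144 × 0.02 = 3 in group B and fewer in group A, so Fisher might be used there. The figures describe the Pearson test only.
- **Category percentages would show direction anyway.** This is true as description, but the P-value beside them would still test a different question.

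**Conclusion.** The point holds as a minor improvement to one secondary analysis. On the natural reading, an ordered outcome is compared with a test that ignores its order. Under a uniform proportional-odds shift with OR 1.5 to 2.0, 144 per arm and two-sided 5%, the cost is about 11 to 18 points of power on the four tabulated distributions. Other plausible distributions and effects widen that range, and some non-uniform shifts reverse its sign.

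A reader might also infer that compliance is the outcome meant to prove the short regimen's advantage. The text does not go that far. Quality of life is named beside compliance in the abstract, the main Discussion adds economic burden and return to everyday life, and no superiority hypothesis is stated for compliance. Nor is the planned test invalid: it holds its type I error, and the primary non-inferiority conclusion does not depend on it.

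**What to change.** In the Statistical analysis section, state that the four-level compliance score at 1 week and 3 months will be compared between arms with the tie-corrected Mann–Whitney (Wilcoxon rank-sum) test. Report with it a common odds ratio from a proportional-odds model, or the probability of better compliance, with a 95% confidence interval, and give the category percentages by arm. Keep chi-square or Fisher's exact test for binary and unordered outcomes such as complications.

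This costs one sentence, needs no new data and uses a test the article already names. It should be settled before compliance is compared between the arms. The downside is less sensitivity to differences that are not a uniform shift, including movement between only two adjacent levels. The category percentages would keep such patterns visible.
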